## Abstract

**Background:** Arts-based health programmes (ABHP) can enhance the physical and psychosocial health and wellbeing of older people. However, the feasibility and usefulness of such programmes in Ireland are currently unknown. The primary aim of this study is to examine the feasibility of the study design, its application to a music and movement for health programme and associated costs. The secondary aim is to obtain preliminary effect estimates of an ABHP on health and wellbeing in older adults.

**Methods:** This study is a pragmatic cluster-randomised controlled feasibility trial. Community-dwelling adults, aged 65 years or older will be recruited in the mid-west region of Ireland via methods including social prescription, traditional and social media. The clusters, based on geographical region, will be block randomised to either the ABHP or control using 1:1 allocation ratio. The programme will comprise a 1.5-hour music and dance session each week for 12-weeks together with a 1-hour home-based music and movement programme for 12-weeks. A qualitative and quantitative process evaluation of the arts-based health programme will be performed.

**Outcomes:** Primary outcomes for feasibility include recruitment rates (the number of participants recruited per cluster per month); retention rate (the number of participants who complete measures at baseline and at follow up post intervention, and minimum average attendance. Secondary outcomes will include physical function, balance, physical activity, loneliness, social isolation, cognition, mood, as well as quality of life and cost.

**Conclusions:** If this pioneering study finds evidence to support feasibility and acceptability, a future larger-scale definitive trial will be conducted to examine the effectiveness of an arts-based health programme for older adults. This research aims to strengthen collaborative efforts to implement effective, sustainable and cost-effective programmes for older adults to support community connection, enhancing health and wellbeing, in turn reducing demands on the healthcare system.

**ISRCTN registration:**
ISRCTN35313497 (18/02/2022).

## Introduction

Ireland’s ageing population is increasing, which is contributing to significant healthcare challenges (
DoH, 2016b). A large proportion (61%) of older adults have a chronic condition (
DoH, 2016b) and are not meeting the recommended physical activity guidelines (
Murtagh *et al.*, 2015). Additionally, the risk of falling increases with age, with one in three older people falling each year (
HSE, 2008), leading to a loss of confidence, and reduction in physical function and social interaction (
Yardley & Smith, 2002). Almost one-third of adults aged 50+ in Ireland report loneliness, which was found to be most prevalent among those over 75 years and those living alone (
Ward *et al.*, 2019). More recently, the consequences of the COVID-19 pandemic and associated public health measures led to increased levels of social isolation, loneliness and physical deconditioning (
Dahlberg, 2021;
Krendl & Perry, 2021;
Robb *et al.*, 2020). Loneliness and social isolation are associated with poor health outcomes comparable to the dangers of smoking and obesity (
Cacioppo *et al.*, 2015;
Perissinotto *et al.*, 2012). The financial and health implications of chronic conditions, falls, low levels of physical activity and loneliness reflect the failure of national frameworks and strategies (
DoH, 2013;
DoH, 2016a;
DoH, 2018;
Ward *et al.*, 2019) to implement preventative strategies effectively (
Frieden, 2010). Such findings reaffirm the need for pioneering projects that are community-based and utilise community resources.

Research demonstrates that older adults tend to prefer physical activity that develop social connections and promote fun as well as increase accessible skills with benefits to their daily lives (
Devereux-Fitzgerald *et al.*, 2016;
O’Regan *et al.*, 2020). Compared to exercising alone, group exercise fosters social cohesion and connectedness, which can lead to greater participation among older adults (
Kattenstroth *et al.*, 2010;
Rivera-Torres *et al.*, 2019). Recent research provides evidence to support arts and creative interventions in improving health; playing a critical role in health promotion; helping to prevent or delay cognitive and physical decline and frailty (
McQuade & O’Sullivan, 2021;
WHO, 2019). Occupation-focused, meaningful, group-based programmes such as dance and music are shown to enhance physical and mental health, wellbeing and belonging (
Shanahan *et al.*, 2017;
Stewart & Irons, 2018). Dance is an art form involving physical exercises such as partnered multidirectional movements, weight shifting and single leg stepping. Systematic reviews have found that dance can improve physical health with positive effects on strength, endurance, functional fitness and some risk factors associated with falls including balance and mobility (
Fernández-Argüelles *et al.*, 2015;
Hwang & Braun, 2015;
Liu *et al.*, 2021). Currently the findings are mixed for gait outcomes (
Fernández-Argüelles *et al.*, 2015;
Liu *et al.*, 2021). Additionally, positive effects have been reported for the effects of dance and dance movement therapy on depression, anxiety, quality of life, interpersonal, cognitive and psychomotor skills (
Koch *et al.*, 2019). However, limitations exist in the current evidence base including small sample sizes, diversity in dance prescription, variable outcomes, the absence of tailoring and participant involvement in the programme design. Music can have an important role in emotion, communication and social interaction in ageing. Indeed, musical activities can support positive ageing. Listening and singing to music have been associated with better emotional well-being, competence and reduction in social isolation (
Hays & Minichiello, 2005). A Cochrane review (
van der Steen *et al.*, 2018) of music-based activities for older people with dementia and a systematic review and meta-analysis (
Zhao *et al.*, 2016), identified that providing at least five sessions of a music-based therapeutic programme may reduce depressive symptoms and may improve emotional well-being, quality of life and reduce anxiety. The literature demonstrates that music and dance can contribute to preventative health and well-being strategies for older people. However, despite the evidence that demonstrates the health benefits of both music and dance for older adults, research examining the physical and emotional benefits as well as the feasibility of a music and dance programme for older adults in Ireland is lacking. Prior to a conducting a large-scale study to examine the effectiveness of music and dance for older adults, a pilot trial is necessary to determine the feasibility and acceptability of the study design and evidence-based, participant-informed arts-based programme.

Consequently, the primary aim of this study will be to examine the trial and intervention feasibility by assessing the recruitment and retention rates, fidelity and acceptability of a co-designed arts-based programme study processes. The secondary aim is to obtain preliminary information to describe the effect of the programme on function, mobility, social isolation, loneliness, physical activity, cognition, mood and quality of life measures in older adults living in the mid-west of Ireland. Drawing on the work of
Crealey & O’Neill (2021), an embedded pilot health economic analysis will also be conducted to analyse the health economic data that will be collected in the feasibility trial and inform the health economics section of any subsequent trial. Ethics approval was granted for the study by the University of Limerick, Faculty of Education and Health Sciences Research Ethics Committee (EHSREC Ref No: 2022_01_08_EHS; Date of Approval: 26/01/2022).

## Methods

The
*Music and Movement for Health* study is a pragmatic cluster-randomised, controlled feasibility trial with an embedded economic evaluation and process evaluation. The methodology was guided by the PRagmatic Explanatory Continuum Indicator Summary-2 (PRECIS-2) tool, which is illustrated in
Figure 1 (
Loudon *et al.*, 2015). Reporting of the trial conforms to the Standard Protocol Items: Recommendations for Interventional Trials (SPIRIT) checklist (
Chan *et al.*, 2013), the CONSORT extension to cluster randomised trials checklist (
Campbell *et al.*, 2012), and the checklist of the Consolidated Standards of Reporting Trials (CONSORT) extension for feasibility and pilot trials checklist (
Thabane *et al.*, 2016;
Thabane & Lancaster, 2019). Completed checklists and other study materials can be found in the
*Extended data* and
*Reporting guidelines* sections (
Clifford, 2022).

**Figure 1. f1:**
[figure not shown]
The Pragmatic-Explanatory Continuum Indicator Summary 2 (PRECIS-2) wheel-Music and Movement for Health (
Loudon *et al.*, 2015). This figure is an original figure produced by the authors for this article.

As evident in
Figure 1, a broad consultative approach was used to ensure our eligibility criteria are appropriate, representative, and inclusive; and exclusion is aligned with usual care considerations. We will use a variety of recruitment strategies and envisage that most of the participants will be recruited via usual pathways, including social prescription by professionals as well as advocacy groups, newspapers and social media. The setting is both community and home based and not a controlled environment. Qualified dance teachers and music therapists will deliver the arts-based programme to participants randomised to receive the programme. The programme will be designed so that it can be integrated and implemented into the community setting. As such, the programme could easily occur in the community without the extensive use of resources. The
*Music and Movement for Health* study contains key ingredients to ensure fidelity in content and delivery but sufficiently flexible to accommodate preferences, skill level and the needs and abilities of the various community cohorts. We are not introducing special measures to incentivise compliance. However, we will monitor participation using a log and include behavioural change techniques (BCTs) to optimise participation in the programme (
Kok *et al.*, 2016). Our primary outcomes are feasibility and acceptability, which are relevant to inform a future definitive trial and the secondary outcomes are relevant to the participants. Our analysis will include data from participants in both intervention and control groups regardless of their level of engagement during the intervention.

### Participants and recruitment

Two transparent expert consultation (TEC) workshops (
Higginson *et al.*, 2013) (EHSREC No: 2021_09_12_EHS) were held with health care practitioners (public health nurses, General Practitioners (GPs), community physiotherapists), music therapists, dance teachers and researchers to produce a stakeholder-informed specification on participant eligibility criteria and recruitment pathways considering inclusivity and safety. As such, those who contributed to the TECs had extensive expertise and experience in rehabilitation, medical care or arts-based programmes (music/dance) for older people living in the community. This method is particularly useful when seeking to generate evidence-based recommendations for promoting the engagement of older people in physical and social activities (
Brighton *et al.*, 2018;
Yardley *et al.*, 2007). The recruitment procedures were also informed by previous research (
O’Donnell *et al.*, 2022), the experience of members of the research team from working on previous studies such as the
*Move for Life* (MFL) programme (
O’Regan *et al.*, 2020), and recommendations from our Patient and Public Involvement (PPI) panel.

### Patient and Public Involvement 

This study embeds Patient and Public Involvement (PPI) in its overall approach and processes. As such, to ensure that the
*Music and Movement for Health* project is informed by those who might engage with the programme now and into the future, a six-member PPI panel was established to support the research programme. This PPI panel has been instrumental in our processes thus far, with membership from:
Age and Opportunity Ireland, Dance Limerick, dance teachers and older adult dancers. To date, PPI actions have included contribution to study design, outcome measures, intervention planning, programme logo, programme title, recruitment strategies and information posters and leaflets. It is anticipated that the future contributions of the PPI panel will include all aspects of research planning and delivery, attending progress meetings; interpreting results; the dissemination and communication of the research findings; and in the creation of a sustainable arts-based intervention. PPI meetings will be held online or face-to-face and members will be compensated for their participation. There are also flexible opportunities for involvement by e-mail, phone and post.

### Inclusion criteria

Community-dwelling older adults 65 years of age and older will be invited to participate in the study. Eligible participants will be able to walk three metres with or without an assistive device, have a basic level of English literacy or an identified person who can translate English to their first language and be able to hear and follow instructions.

### Exclusion criteria

To ensure participants are safe to exercise they will be excluded if they
*subjectively* report health conditions that contraindicate their participation in exercise such as having had an acute stroke (within the past three months) or have an unstable neurological, cardiac or respiratory condition (or are on oxygen therapy). Participants will be excluded if they do not satisfy the requirements of the Physical Activity Readiness Questionnaire (PAR-Q). The PAR-Q is a screening tool that contains seven questions to determine whether individuals are safe to engage in exercise and become more physically active based on health history, current symptoms, and risk factors (
Shephard, 2015).

### Screening

People who are interested in the study will contact a member of the research team, who will answer any queries about the research study and screen to ensure they fulfil the eligibility criteria. Following this, eligible participants will be provided detailed written information about the study, a consent form, and the PAR-Q to complete. The PAR-Q was identified as a sensible tool to ensure participants are safe to take part in the music and movement for health programme. If a participant responds positively to any of the questions on the PAR-Q, they will be required to contact their General Practitioner (GP) to ensure they are deemed medically safe to participate in the programme. On attending the baseline assessment, a member of the research team will answer any queries and collect the signed and completed consent form and PAR-Q. Furthermore, at the baseline assessment participants will be asked about their medical history, physical function, past falls incidence and any medical attention received due to a previous fall.

The team originally planned to use the Montreal Cognitive Assessment Score (MoCA) (
Hobson, 2015) as a cognitive screening tool. However, an outcome of the TEC workshops was to remove a cognitive screening tool cut-off level from the exclusion criteria, as it may exclude people who could participate and benefit from the
*Music and Movement for Health* intervention. Instead, we will obtain information on cognition at baseline and follow-up using the Trail Making Test to obtain information about mental flexibility, executive functioning, visual searching and processing speed. This tool is also reported to be sensitive to detecting several cognitive impairments, however a cut-off score will not be used (
Cangoz *et al.*, 2009).

In addition, a tool will not be used to screen for literacy level. Instead, participants will be advised that they will be required to complete a number of questionnaires and that an assessor would be available at each station to support each participant as required. During the baseline assessment, we will obtain participants highest level of education as part of the demographic questionnaire.

### Recruitment

A purposive sampling strategy will be used to recruit older people for the 12-week
*Music and Movement for Health* programme. For the 12-week programme, we plan to recruit individuals in the Mid-West of Ireland from a minimum of six geographical regions across three counties (Limerick, Clare and Tipperary) in the Mid-West of Ireland. Limerick city and county was reported to have the second highest level of total income per person in the State, after Dublin in 2014. However, Limerick also has more areas of deprivation and a lower labour force skillset profile compared to other cities; with the highest number of unemployment blackspots in which 35.7% of the workforce declared themselves unemployed. Limerick also has the lowest number of recreational facilities nationally. Recreational opportunities may also be more difficult to access in more marginalised or rural areas (
CSO, 2016). In 2016, approximately 65% of people in county Clare lived outside of larger towns (towns with more than 1,500 people) (
Clare County Council, 2018). Tipperary is one of the most populated rural counties in Ireland, with a strong network of vibrant and robust towns and villages with service centres provided at strategic locations throughout the county. There are many areas in Tipperary with an ageing population and over 25% of the population aged over 65 years live alone (
Tipperary County Council, 2021). In line with other studies (
O’Donnell *et al.*, 2022), every effort will be made to achieve a gender balance amongst the participants through our recruitment strategies, including recruitment sites and poster images. For this study, participants will be recruited through social prescription (e.g., public health nurses, GPs, physiotherapists and occupational therapists), adverts in community areas (church bulletins, local sports clubs, the Gaelic Athletic Association) and local newspapers, linking with volunteer organisations, primary care centres and community centres, contacting community-based projects such as men’s sheds and word of mouth vis-à-vis the use of social media. Each centre will be selected for their ease of access for local community members, parking facilities, recreational facilities (tea/coffee availability), suitability for the programme (space and floor type) and ease of mobility within the building itself (flights of stairs etc.).

### Sample size

As our primary outcomes are feasibility it is desirable to keep the sample size small enough to allow close monitoring of participants and the programme while large enough to obtain sufficient data on our primary outcomes of feasibility. For feasibility reasons we will ensure we have sufficient numbers in each group to generate a ‘group’ climate likely to maximise adherence. Hence if the group gets too small, it becomes unviable for participant engagement and sense of community. The minimum numbers required to sustain a community-based music and movement programme and maintain the required group dynamics is between 10–12 older adults per group; guided by practice expertise within the research team and previous feasibility studies (
Clifford *et al.*, 2021;
O’Regan *et al.*, 2020). The primary feasibility outcomes will be evaluated by assessing recruitment rates (the rate of participants recruited to the study); retention rate (the number of participants who complete measures at baseline and at follow up post intervention) and minimum average attendance (number of participants who attended at least 65% of the intervention sessions). Hence, we aim to recruit a minimum of 72 participants in total (n=12 per cluster) allowing for 20% attrition (n=60; n=10 per cluster), we will be able to estimate a recruitment rate of 60% within a 95% confidence interval +/- 12.6%; a retention rate of 80% within a 95% confidence interval of +/- 10.3% and a minimum average attendance of 65% within a 95% confidence interval of +/- 12.3%. 

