### Randomisation

Pragmatic randomised controlled trials (RCTs) are conducted to answer the important question of how an intervention works in real-world contexts in a heterogeneous real-world population. Thus, we plan to recruit individuals in the Mid-West of Ireland from at least six geographical regions or clusters; the groups of study participants are the units of randomisation (clusters), and individuals within these groups are the units of analysis. The clusters are based on the geographical regions where the participants reside (two clusters in each county n=6 geographical regions, with n=2 additional reserve clusters sites). Using block randomisation, the clusters will be randomised to either the intervention or control (usual care) using 1:1 allocation ratio. Thus, there will be an intervention and a control group in each county. Given the wide geographical spread of these locations, it would be impractical to conduct an RCT by randomising participants individually to either the intervention or control arm and then find a central location to conduct the intervention. Additionally, this approach would not keep the community groups together. The cluster RCT design will ensure we keep community groups together. Research from a recent cluster-randomised controlled study, demonstrated that being ‘
*part of a local community group*’ can afford additional benefits, including an increased likelihood to remain active due to the friendships they had formed (OR=3.04, 95% CI=1.65–5.60, p=0.001), as a result of attending of the programme (
O'Regan *et al.*, 2021). In line with our pragmatic approach the study will have two phases for recruitment and two implementation blocks as the intervention can apply naturally to the group. Participants in the same group will receive the same intervention, thus approximating clinical practice, and producing generalisable findings.

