	To explore the differences between the groups for Physical Function, Balance, Physical Activity, Loneliness, Social Isolation, Mood, and Quality of Life.	Results for each outcome of interest.	We can determine the required sample size for a definitive trial.	ICC (intraclass correlation coefficient) will be used to calculate the design effect. Thus, the required sample size for a CRCT (cluster-randomised controlled trail) will be calculated by multiplying the required sample size for the equivalent ungrouped study with the DE.
	Pilot economic analysis to assess costs and inform a definitive trial.	A pilot economic analysis to inform the design and conduct of a full economic evaluation to assess the cost effectiveness of the programme developed.	The methods developed and implemented for the conduct of the pilot health economic analysis proved to be feasible and acceptable to study participants.	The criterion for success includes obtaining sufficient data on cost. Incremental analysis to calculate the mean differential in costs and QALYs. The incremental cost effectiveness ratio (ICER) will be calculated and analysed. Parametric and probabilistic analyses will be employed to explore uncertainty.

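### The stated precision of the primary feasibility outcomes allows nothing for clustering: it is too narrow for attendance, and for retention and recruitment only above an ICC of about 0.02 and 0.06

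*Protocol article*

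**What the plan says.** The Sample size section sets the recruitment target: "we aim to recruit a minimum of 72 participants in total (n=12 per cluster) allowing for 20% attrition (n=60; n=10 per cluster". It then claims three precisions, all in percentage points. For recruitment it says: "we will be able to estimate a recruitment rate of 60% within a 95% confidence interval +/- 12.6". The corresponding half-widths are 10.3 points around 80% for retention, and 12.3 points around 65% for attendance. It names no ICC or design effect and does not say that clustering has been set aside. The same section sizes the groups so that a group atmosphere forms which should support adherence.

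The Randomisation section describes "two clusters in each county n=6 geographical regions, with n=2 additional reserve clusters sites" and says that "the clusters will be randomised to either the intervention or control (usual care) using 1:1 allocation ratio". It gives keeping community groups together as a reason for the design, and it names individuals as the units of analysis.

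The Assessment procedures section defines the proportions. Recruitment is enrolled people over those who expressed interest. Retention is taken over recruited participants. The Sample size section defines attendance by the intervention sessions attended.

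Table 1 says that "ICC (intraclass correlation coefficient) will be used to calculate the design effect", but only for sizing the definitive trial. The Data analysis section makes confidence interval estimation a focus and does not mention clustering.

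**The concern.** A 95% half-width computed as if every participant were independent is correct only if the ICC is zero. The protocol gives a reason to doubt that for attendance at least, since it expects the group itself to influence adherence. It also plans to estimate an ICC for the next trial. With positive correlation within groups, 58 or 72 people in six clusters carry less information than the same number of unrelated people.

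Recruitment, retention and attendance are the primary outcomes, and retention and attendance have targets of 80% and 65%. A half-width that is too small overstates how well the trial can show whether those targets are met. The precision claim is an affirmative statement in the protocol, so it is not a detail left to a later analysis plan.

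**Working it through.** **Inputs.** From Sample size: 72 recruited, 12 per cluster; 60 after attrition, 10 per cluster; proportions 0.60, 0.80 and 0.65; 95% confidence. From Randomisation: six clusters allocated 1:1, so three per arm. From Assessment procedures and Sample size: the definitions of each proportion. The ICC is not given; 0.01 to 0.10 is assumed here.

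**Step 1: reproduce the printed figures.** Half-width = 1.96 × √(p(1−p)/n). With 20% attrition, 72 × 0.8 = 57.6, rounded to 58:

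- recruitment: 1.96 × √(0.60 × 0.40/58) = 12.61
- retention: 1.96 × √(0.80 × 0.20/58) = 10.29
- attendance: 1.96 × √(0.65 × 0.35/58) = 12.28

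These round to the printed 12.6, 10.3 and 12.3. The printed n = 60 gives 12.40, 10.12 and 12.07, which does not match. A t quantile with n = 60 gives 12.66, 10.33 and 12.32, which misses the first figure by rounding. Both the match and the near match imply a design effect of 1. The figure 58 is inferred: the text prints 60, and 60 of 72 is 16.7% attrition, not 20%.

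**Step 2: use the denominators that the protocol defines.**

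- Recruitment: if 72 enrolled is 60% of those interested, 72/0.60 = 120 people, or 20 per cluster if evenly spread. Half-width without clustering: 8.8.
- Retention: 72 recruited, 12 per cluster. Half-width without clustering: 9.2.
- Attendance: only the intervention arm has sessions, so 36 people in three clusters of 12. Half-width without clustering: 15.6.

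**Step 3: add the design effect.** DE = 1 + (m−1) × ICC, with equal cluster sizes m; multiply each half-width by √DE.

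| Outcome | n, m | Printed | ICC 0 | ICC 0.01 | ICC 0.05 | ICC 0.10 |
|---|---|---|---|---|---|---|
| Recruitment | 120, 20 | 12.6 | 8.8 | 9.6 (DE 1.19) | 12.2 (DE 1.95) | 14.9 (DE 2.90) |
| Retention | 72, 12 | 10.3 | 9.2 | 9.7 (DE 1.11) | 11.5 (DE 1.55) | 13.4 (DE 2.10) |
| Attendance | 36, 12 | 12.3 | 15.6 | 16.4 (DE 1.11) | 19.4 (DE 1.55) | 22.6 (DE 2.10) |

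**Step 4: find the ICC at which each printed figure becomes too narrow.** Solve ICC = ((printed/unadjusted)² − 1)/(m−1).

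- Recruitment: ((12.6/8.765)² − 1)/19 = 1.066/19 = 0.056, about 0.06.
- Retention: ((10.3/9.239)² − 1)/11 = 0.243/11 = 0.022, about 0.02.
- Attendance: the printed 12.3 is already below 15.6 at ICC 0, so it is too narrow at every non-negative ICC.

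**Step 5: small number of clusters.** The table uses the normal quantile, which is optimistic here. With six clusters, a t quantile on 5 degrees of freedom widens an interval by about 1.3 times (12.6 becomes 16.5). With three clusters and 2 degrees of freedom the factor is 4.303/1.96 = 2.2.

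**The case against.** The printed arithmetic is right for its assumption, and at an ICC of 0.01 clustering adds less than 1 point to any of the three half-widths. The size of the effect rests on an ICC that the document does not give. Both points stand, and they make the conclusion conditional.

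A reader might infer that the precision is overstated for every primary outcome. The documents do not support that. On the defined denominators, the recruitment and retention figures are conservative at ICC 0.01, and recruitment still is at 0.05 (12.2 against 12.6).

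A reader might also put the whole attendance shortfall down to clustering. The step from 12.3 to 15.6 comes from counting both arms for an outcome that exists in one; only the rest is a design effect. Applying the 2-df t quantile at ICC 0.05 gives about ±43 points, but around 65% that runs past 100%. It shows how little three clusters can say and is not a usable interval.

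The stated link between group and adherence bears directly on attendance in intervention groups. It bears less on recruitment, which precedes the sessions, or on retention in usual-care clusters. The Table 1 design effect concerns clinical outcomes in the next trial, so the contrast shows awareness of clustering, not a direct contradiction.

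Finally, the Data analysis section fixes no variance formula, so it cannot be said that the reported intervals will ignore clustering. The 80% and 65% targets carry no stated rule based on a confidence limit, so no stated decision is shown to change. Group size is also justified by viability at 10–12 people. None of this rescues the precision statement as written.

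**Conclusion.** The point holds in a limited form. All three half-widths were computed without a clustering term, and they match n = 58, which the protocol does not print. For attendance the claimed 12.3 points is wrong whatever the ICC: 15.6 before clustering and about 16.4 to 22.6 for ICCs of 0.01 to 0.10. For retention the claim is too narrow only above an ICC of about 0.02, and for recruitment only above about 0.06.

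These results assume equal cluster sizes, full recruitment of 72, about 120 people expressing interest, attendance read as a proportion of participants, and an ICC range chosen for illustration. The defect lies in the sample size justification. It does not invalidate the trial and is no argument that the trial needs more participants.

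**What to change.** In the Sample size section, restate each half-width on its own denominator (about 120 expressing interest, 72 recruited, 36 in the intervention arm), multiplied by √(1 + (m−1) × ICC) over a stated ICC range such as 0.01 to 0.10. Say that normal-based intervals are optimistic with three to six clusters. Reconcile the printed 60 with the 58 that the figures imply.

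For the analysis, compute the reported retention and attendance intervals with a cluster-based variance and a small-sample correction (cluster proportions or a corrected robust standard error), and show the proportion in each cluster.

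The cost is a few sentences or a small table and little extra analysis code. The stated precision becomes less favourable, most visibly for attendance. No participants are added and the design is unchanged.
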